## Abstract

**Background:**

Chronic diseases are the principal cause of morbidity and mortality worldwide. An increased consumption of vegetables and fruit reduces the risk of hypertension, coronary heart disease, stroke, and cancer. An increased fruit and vegetable (FV) intake may also prevent body weight gain, and therefore indirectly affect type 2 diabetes mellitus. Insufficient physical activity (PA) has been identified as the fourth leading risk factor for global mortality. Consequently, effective interventions that promote PA and FV intake in a large number of people are required.

**Objective:**

To describe the systematic development of an eHealth intervention, MyPlan 1.0, for increasing FV intake and PA.

**Methods:**

The intervention was developed following the six steps of the intervention mapping (IM) protocol. Decisions during steps were based upon available literature, focus group interviews, and pilot studies.

**Results:**

Based on needs assessment (Step 1), it was decided to focus on fruit and vegetable intake and physical activity levels of adults. Based on self-regulation and the health action process approach model, motivational (eg, risk awareness) and volitional (eg, action planning) determinants were selected and crossed with performance objectives into a matrix with change objectives (Step 2). Behavioral change strategies (eg, goal setting, problem solving, and implementation intentions) were selected (Step 3). Tablet computers were chosen for delivery of the eHealth program in general practice (Step 4). To facilitate implementation of the intervention in general practice, GPs were involved in focus group interviews (Step 5). Finally, the planning of the evaluation of the intervention (Step 6) is briefly described.

**Conclusions:**

Using the IM protocol ensures that a theory- and evidence-based intervention protocol is developed. If the intervention is found to be effective, a dynamic eHealth program for the promotion of healthy lifestyles could be available for use in general practice.

## Introduction

Chronic diseases, such as cardiovascular disease, type 2 diabetes, and cancer, are the principal cause of morbidity and mortality worldwide, representing 68% of all deaths [1]. An increased consumption of vegetables and fruit reduces the risk of hypertension, coronary heart disease, stroke, and cancer. Furthermore, an increased fruit and vegetable (FV) intake may also prevent body weight gain, and therefore indirectly affect type 2 diabetes mellitus [2]. Insufficient physical activity (PA) has been identified as the fourth leading risk factor for global mortality [3]; it accounts for 6% of all deaths per year, and accounts for 21-25% of breast and colon cancers, 27% of diabetes, and 30% of ischemic heart disease worldwide [4,5]. Consequently, effective interventions that promote PA and FV intake in a large number of people are required. Reviews have shown that eHealth interventions are effective in changing PA and FV intake [6,7]. In eHealth interventions, information and communication technologies are used to improve or enable health and health care [6]. eHealth interventions allow a personalized approach at a relatively low cost by making use of interactive, computerized technologies [6,8], and have several advantages: reduced personal demands, consistency over time, increased interactivity and flexibility, automated data collection, and more honest self-report. Most of these interventions are delivered through the Internet only [6,9,10]. Although a large number of people can be reached through the Internet, the percentage of individuals who start with an Internet-delivered intervention is low, and sustained use is even lower [11]. Reach and use of eHealth interventions can be enhanced by the provision of additional support [11]. General practitioners (GPs) may be influential in supporting patients by providing extra information when implementing the intervention [12-14]. The reach and sustained use of eHealth interventions may also be increased by using computer-tailored feedback and facilitating goal setting and self-monitoring, as well as by incorporating email and short message service (SMS) text message reminders as behavior change methods into eHealth interventions [15-17]. Although eHealth interventions have been shown to be effective, effect sizes of eHealth interventions that target PA and dietary behavior are small [16,18]. Computer-tailored feedback merely targets variables that primarily address the adoption of an intention to change (eg, attitude or social norm), hence leaving many individuals in an intention-behavior gap. It is also important to address this gap by addressing postintentional factors (eg, action planning and problem solving). A self-regulation perspective may be well suited to integrate both pre- and postintentional processes, and to develop interventions that guide individuals during all phases of behavior change [19,20]. Self-regulation techniques can empower adults and allow them to make more autonomous decisions about their own health behavior [19,21,22]. Self-regulation is a goal guidance process which occurs in a motivational and volitional phase [19]. During the motivational phase (ie, goal selection, goal setting, and representation), participants become aware of risks, form intention-to-change behavior, and set goals to change their behavior. In the volitional phase (ie, active goal pursuit, goal attainment, and maintenance or goal disengagement), participants make action plans, engage in goal pursuit, and maintain or adapt their goals [19].

In this study, a dynamic eHealth intervention, MyPlan 1.0, was developed that targets self-regulation processes to increase PA and FV intake. To enhance reach and use, the intervention will be implemented in general practice. To ensure that MyPlan 1.0 is theory and evidence based, as well as feasible for implementation in general practice, the intervention mapping (IM) protocol was used as the planning model for the intervention [23]. IM facilitates effective decision making by formalizing the development process of the intervention in six steps [23]. Via the IM protocol, researchers are guided in selecting target behaviors (Step 1), specifying intervention goals (Step 2), choosing intervention strategies (Step 3), and developing intervention tools and programs (Step 4). IM also involves the planning of the implementation (Step 5) and the evaluation (Step 6). This paper describes the theoretical considerations and decisions made during each step of the IM protocol. This resulted in a detailed intervention description, which provides insight into the design and different components of the intervention, and will help planners to identify techniques and replicate the different intervention components [24].

## Methods

The IM protocol consists of the following six steps: (1) needs assessment, (2) development of matrices of change, (3) selection of theory-based methods and practical applications, (4) description of the program production, (5) development of a program adoption and implementation plan, and (6) completion of an evaluation plan [23].

In Step 1, a planning group was established to ensure that the intervention targets important factors to increase effectiveness and sustained used of the eHealth intervention. Based on the needs assessment, we also selected the target behaviors in Step 1.

In Step 2, we adopted self-regulation theories to determine the intervention content and to formulate performance objectives. Different statements were formulated about how participants may achieve the intervention goals. These statements are specific actions that have to be taken by participants and are called performance objectives [23]. Next, relevant and changeable determinants of the target behavior were selected in the second step. Finally, change objectives were formulated by stating what needs to be changed regarding a determinant in order to accomplish a performance objective.

In Step 3, theory-based methods that can modify the selected determinants to achieve the performance objectives were determined. Matching methods were selected based upon the results of systematic reviews that summarized the effectiveness of behavior change methods for healthy eating and physical activity interventions. We also took into account the summary list published by Bartholomew et al [23] and the taxonomy of behavior change techniques published by Abraham and Michie [24].

In Step 4, an intervention plan was developed, based on the selected methods and practical applications. Previous programs that were effective were used as examples [25-28]. Furthermore, a pretest of the intervention was conducted in Step 4 to identify possible elements of improvement and to evaluate the feasibility and user-friendliness of the intervention program.

In Step 5, the implementation of the intervention was planned. Support by general practitioners has been shown to improve the use and the effect of computer-tailored programs [11]. Therefore, GPs were involved in the implementation of MyPlan 1.0 in general practice. To this end, during Step 5, we conducted focus group interviews with GPs regarding the implementation.

The aim of this paper was to describe the intervention development. It is therefore not a research protocol of the trial, which is reported at ClinicalTrials.gov (trial registration number: NCT02211040). Therefore, in Step 6, we only specify the evaluation design and briefly describe the evaluation plan. We briefly describe the decisions made during each step of the IM protocol in the results section.

## Results

### Step 1: Needs Assessment

The planning group consisted of six researchers from different health disciplines—physical activity, nutrition, psychology, and primary health care—and leading GPs from the Belgian association of GPs, who are potential end users of the program. The core theories, methods, practical applications, implementation options, and evaluation strategies were discussed among this planning group.

Based on needs assessment, physical activity and fruit and vegetable intake were selected as target behaviors. Insufficient physical activity and unhealthy diet are two important risk factors of chronic diseases (eg, diabetes and ischemic heart diseases) and cancers (eg, breast and colon cancer) [1,29]. Adults are recommended to have 30 minutes of moderate-intensity aerobic PA 5 days per week, or to have 20 minutes of vigorous-intensity aerobic PA 3 days per week [30]. However, these recommendations are not reached by a large part of the population [5], nor by a majority of Belgian adults (62%) [31]. Therefore, it was decided to target physical activity levels in various subdomains (eg, activities at work, activities during leisure time, and active transports and sports).

Adults are recommended to consume at least five portions or 400 grams of fruit and vegetables a day, and data from the World Health Survey showed that 78% of the adult population consumed less than five portions of fruit and vegetables daily [32,33]. Western adults (ie, in Belgium, Luxembourg, France, Ireland, the Netherlands, and Great Britain) consume on average 129 grams of fruit and vegetable per day [2]. Furthermore, an evaluation of the gap between food-based dietary guidelines and the usual food consumption in Belgium indicated that fruit and vegetable consumption was significantly lower than recommended in a large part of the Belgian population. Of Belgian adults, 53% and 62% do not eat fruits and vegetables on a daily basis, respectively [34]. Therefore, we also decided to focus on fruit and vegetable intake as a dietary component of the intervention. After the needs assessment, the intervention goals were as follows: (1) to increase fruit and vegetable intake, and (2) to increase physical activity levels in Belgian adults (older than 18 years).

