In total, 30 adults will be selected in each of 15 general practices (n=450). First, a researcher will select 10 patients that will be allocated to the intervention group and 10 patients that will be allocated to the control group. Next, GPs will be asked to recruit another 10 patients to complete the intervention program. In this way, it can be evaluated whether GPs' involvement leads to more sustained use of the eHealth intervention, and higher levels of PA and FV intake. In both intervention groups, adults will be invited to complete session 1 either on a tablet in general practice or on their computer at home. Adults who do not use the tablet have to fill out a short questionnaire and leave their email address to be sent a reminder email to complete session 1 at home. After 1 week and 1 month of completing session 1, adults will receive an email to respectively start sessions 2 and 3. In the control group, adults will have to fill out a questionnaire at baseline in general practice or at home and at 1-month postintervention. To prompt adults to complete all questionnaires and sessions, reminder mails and SMS text messages will be sent. Inclusion criteria for participating in the study in both intervention and control groups are as follows: at least 18 years old, understand Dutch language, have an email address, and have access to the Internet. The outcome measures—increase in PA level, increase in FV intake, and self-regulation skills from baseline to postintervention—will be compared for the control and intervention conditions by conducting repeated measures multivariate analyses of variance (MANOVAs). Participant characteristics (ie, socioeconomic status [SES], age, sex, health status, and reaching health norms) will be compared at baseline. Characteristics that differ for the intervention and control groups will be added as covariates in further analyses. Furthermore, multilevel analyses will be conducted to take into account the clustering of participants into general practices.

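### Baseline norm status enters the model only if the groups happen to differ on it, and no planned estimate shows whether the effect differs between adults below and at the norm

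*Protocol article*

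**What the plan says.** Step 1 (Needs Assessment) sets out the recommendations for PA and for combined FV intake and then shows how many adults miss them. For PA: "these recommendations are not reached by a large part of the population [5], nor by a majority of Belgian adults (62%) [31". For FV, from the World Health Survey: "78% of the adult population consumed less than five portions of fruit and vegetables daily". The intervention goals that follow are stated for adults in general, for example "to increase physical activity levels in Belgian adults (older than 18 years".

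Step 6 (Evaluation of the Program) sets the entry criteria as "at least 18 years old, understand Dutch language, have an email address, and have access to the Internet". None concerns current PA, FV intake or norm status. The outcomes are increases in PA, FV intake and self-regulation skills, which "will be compared for the control and intervention conditions by conducting repeated measures multivariate analyses of variance (MANOVAs". Norm status is among the participant characteristics listed for a baseline check: "reaching health norms) will be compared at baseline". The rule for using them is: "Characteristics that differ for the intervention and control groups will be added as covariates in further analyses". Step 6 also says that a researcher randomly allocates patients to Group 1 (intervention) or Group 2 (waiting-list control), whereas Group 3 is recruited by GPs.

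**The concern.** There are two linked issues.

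The first is the covariate rule. Whether someone already meets the norm is a coarse version of the baseline outcome, so it probably predicts change over the month: those above a threshold have less room to rise and tend to regress downward. With random allocation, any Group 1 v Group 2 difference on it is due to chance. A rule that adjusts only when a difference is seen makes the form of the analysis depend on that chance, and it forgoes precision in the other cases.

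The second is interpretation. The behaviours were chosen because of a shortfall, and session 1 feedback compares each person with the norm. Norm status is therefore the effect modifier that the programme's own reasoning suggests first. A covariate main effect, even when it enters, cannot show whether the effect differs by norm status; only a group-by-norm-status term can. If the pooled effect is small, which the Introduction leads one to expect of eHealth programmes, the reader cannot tell a uniformly small effect from a larger one confined to adults below the norm. A later look by norm status would be post hoc.

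**Working it through.** **Inputs from the article**
- Sample size (Step 6): 15 practices × 30 = 450, which reproduces the stated total; 15 × 10 = 150 per group. The article states no alpha, power, effect size, SD or intracluster correlation.
- Share below the norm, *p* (Step 1): PA 0.62 (Belgian adults); FV 0.78 (World Health Survey, not specific to Belgium). Hence 1 − 0.62 = 0.38 and 1 − 0.78 = 0.22 at the norm.

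**Assumptions**
- The population shares apply to the enrolled sample.
- Two-sided 5% test, equal SD, normal approximation, no clustering, no dropout, everyone analysed for each behaviour.
- *r* = effect at the norm ÷ effect below it. The documents give no value, so a range is shown.

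**1. The covariate rule.** The chance difference between Groups 1 and 2 in the share below the norm has standard error √(2*p*(1 − *p*)/150).
- PA: √(2 × 0.62 × 0.38/150) = 0.056, or 5.6 percentage points.
- FV: √(2 × 0.78 × 0.22/150) = 0.048, or 4.8 points.

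The article does not say how a difference is judged. If it is by a 5% significance test, randomisation alone triggers adjustment about 5% of the time. In the other 95% norm status is left out, although imbalances of up to about 1.96 × 5.6 = 11 points (PA) would go unadjusted.

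**2. Pooled effect relative to the below-norm effect.** Ratio *m* = *p* + (1 − *p*)*r*.

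| *r* | PA *m* | FV *m* |
|---|---|---|
| 0 | 0.62 | 0.78 |
| 0.25 | 0.715 | 0.835 |
| 0.5 | 0.81 | 0.89 |
| 1 | 1 | 1 |

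The largest reduction, at *r* = 0, is 38% for PA and 22% for FV. At *r* = 1 there is none.

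**3. Power.** Take an illustrative below-norm effect *d* = 0.30 SD. Power ≈ Φ(effect × √(*n*/2) − 1.96). The pooled comparison uses *n* = 150 and effect *md*. The below-norm comparison uses *n* = 150*p* (93 for PA, 117 for FV) and effect *d*.

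| *r* | PA pooled | PA below norm | FV pooled | FV below norm |
|---|---|---|---|---|
| 0 | 36% | 53% | 53% | 63% |
| 0.25 | 46% | 53% | 58% | 63% |
| 0.5 | 56% | 53% | 64% | 63% |
| 1 | 74% | 53% | 74% | 63% |

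The two have equal power when *m* = √*p*, that is *r* = (√*p* − *p*)/(1 − *p*):
- PA: (0.787 − 0.62)/0.38 = 0.44.
- FV: (0.883 − 0.78)/0.22 = 0.47.

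If adults at the norm respond more strongly than that, the pooled comparison is the more powerful.

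**4. Power of the interaction term.** In the most favourable case (*r* = 0, *d* = 0.30) the difference between strata is 0.30 SD.
- PA, 93 and 57 per group: SE = √(2/93 + 2/57) = 0.238; 0.30/0.238 = 1.26; power about 24%.
- FV, 117 and 33 per group: SE = √(2/117 + 2/33) = 0.279; 0.30/0.279 = 1.08; power about 19%.

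A non-significant interaction would therefore say little, so the stratum estimates and intervals must carry the information.

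**The case against.** The strongest reply is that nothing in the article is contradictory. The goals are stated for adults generally, entry matches them, and the pooled comparison estimates the effect in that population. This stands: the pooled effect is neither biased nor the wrong target.

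A reader might infer that adults already at the norm do dilute the effect, so that they should be excluded or the below-norm effect made a key result. The documents do not support this. They give no effect by norm status. Feedback against the norm is only one component; goal setting, self-monitoring and review of one's own goals need no shortfall. Table 1 includes moving goals to a higher level, and Table 3 includes harder or additional goals. The shares at the norm are population figures, and because participants choose their own module, the share within each may be higher or lower. Step 1 also cites a mean intake of 129 g against the 400 g recommendation, which hints that fewer than 22% meet the FV norm in this setting.

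It can also be said that the Methods section calls the article not a research protocol, so a subgroup analysis may be planned elsewhere. That is fair for the interaction term, and its absence alone would be no finding. It does not excuse the covariate rule, which the article states. The rule has some sense for the GP-recruited Group 3, where differences need not be chance, but little for Group 1 v Group 2.

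**Conclusion.** The concern holds in a limited form. The stated covariate rule is a poor one for the randomised comparison: it ties use of a probably prognostic variable, already collected, to chance imbalance. That norm status predicts change is an inference from its being derived from the baseline outcome; the article does not quantify it.

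The pooled effect may understate the effect in adults below the norm. The 38% (PA) and 22% (FV) are upper bounds that need both no change in adults at the norm and population shares that carry over to the sample. Beyond a relative response of roughly 0.44 to 0.47 the below-norm estimate has no power advantage. The power figures also ignore clustering, dropout and choice of module, so they show the pattern and are not forecasts. An estimate by norm status is worth having as a labelled secondary analysis, not as a replacement for or rival to the all-participant result.

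**What to change.** In Step 6, or in the full protocol or analysis plan if it follows the same rule:

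1. Keep the all-participant comparison as it is.
2. Include baseline norm status in the Group 1 v Group 2 model in all cases, replacing the condition that it must differ at baseline. Let it act on change (norm status by time in the repeated measures model), since the comparison is of change. Use the PA norm for PA and the combined FV norm for FV intake; Step 1 gives no separate norms for fruit and for vegetables.
3. Prespecify a group-by-norm-status term on change, labelled secondary, for PA and for combined FV intake. Report the effect with its interval both below and at the norm, and state that the interaction test has low power.

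Entry criteria, sample size and data collection are unchanged, because norm status is already compared at baseline. The cost is analysis wording and one extra, less precise secondary estimate per behaviour. No power is gained from the below-norm estimate if adults at the norm respond about half as strongly or more.

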### Step 2: Performance Objectives, Determinants, and Change Objectives

The performance objectives for the target PA are shown in Table 1, and those for fruit and vegetable intake are shown in Multimedia Appendix 1. For example, the first performance objective for PA is “Adults recognize the importance of increasing PA levels.”

**Table 1 table1:** Performance objectives for physical activity.

Phases		Performance objectives
**Motivational phase**		Goal selection, setting, and representation
	Performance objective 1	Adults recognize the importance of increasing physical activity levels
	Performance objective 2	Adults decide to change their physical activity levels and set physical activity goals
**Volitional phase**		Active goal pursuit
	Performance objective 3	Adults choose their own strategies to change their physical activity levels
	Performance objective 4	Adults start pursuing their physical activity goals
	Performance objective 5	Adults monitor and evaluate their physical activity levels
	Performance objective 6	Adults maintain or adapt their physical activity goals to a higher level
	Performance objective 7	Adults adapt their goals and strategies when they are unable to reach their initial goals

The health action process approach model of Schwarzer [20] was used to identify and categorize determinants within a self-regulation framework. This model has been successfully applied to predict fruit and vegetable intake [35,36] and physical activity [20,37-40]. The model categorizes determinants into two phases: a motivational phase and a volitional phase [20]. In the former phase, risk awareness, outcome expectancies, and preaction self-efficacy are determinants that influence intentions. After an intention is formed and goals are set, participants try to achieve their goals. In the volitional phase, action planning, coping planning, maintenance self-efficacy, and social support are determinants that influence actual changes in fruit and vegetable intake and physical activity levels. Maintenance and recovery self-efficacy are important determinants for participants to choose to maintain or adapt their goals, based on an evaluation of their behavior change [20].

All performance objectives, related change objectives, and determinants for the target behavior PA are shown in Multimedia Appendix 1. For example, to accomplish performance objective 2—“Adults decide to change their PA level and set PA goals in one or more subdomains”—change objective 2.5—“Adults identify for which PA goals they have the highest level of confidence”—describes what needs to be changed regarding the determinant *preaction self-efficacy*.

